#### Mediators

To optimize interventions in terms of efficiency and effectiveness, treatment-specific and nonspecific working mechanisms should be identified that account for each intervention’s effect on fatigue. Knowledge about these mechanisms is an important prerequisite for improving the efficiency of interventions by shifting focus or shortening the intervention. Also, effectiveness can be increased by improving and tailoring the relevant items, subjects, or exercises, as well as improving the way these are embedded in the intervention. Therefore, the second objective of this study will be to identify the working mechanisms underpinning the interventions.

By using a 3-armed randomized design, it is possible to study both treatment-specific (differentiating) and nonspecific working mechanisms. Also, by assessing important factors multiple times during the intervention, important time-specific information can be acquired.

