#### Mental Health

Mental health will be assessed from the results of 2 questionnaires: the Positive and Negative Affect Scale (PANAS [52]) and the HADS [58], both of which are included in an item bank for cancer survivors [59]. The PANAS consists of 20 items that score on a 5-point Likert scale and has 2 subscales: positive and negative affect. The HADS consists of 14 items on a 4-point scale, has been validated for a Dutch-speaking population [60], and has previously been used to assess psychological distress in cancer patients [61]. Mental health will be assessed at T0a, T1, T2, and T3.

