	Self-efficacy on activities	Selected items from the self-efficacy scales of Bandura [71] and Rodgers [72,73]: 13 items on a 0-100 NRS; subscales: planning and coping.	b		x		
	Catastrophizing	Fatigue Catastrophizing Scale [74,75] 9 selected items on a 5-point Likert scale.	b		x		
	Fear of cancer recurrence	Two selected items on a 7-point Likert scale [76].	b		x		
	Causal attributions	One self-conceptualized open answer question that translates to: “What do you consider as the cause of your fatigue?”	b		x		

^a^Baseline assessment T0 consists of 3 time-points: T0a: before eligibility check, T0b: after inclusion, and T0c: after randomization. T0c’ is assessed after preferential allocation.

^b^Mi and Mi’ = assessments at week (i=) 1, 2, 3, 4, 6, 9 of the intervention

^c^All physical activity measurements are blind except for the experimental activity feedback condition at M3, M6, and M9. In the second semester, M3’, M6’, and M9’ do not include a physical activity measurement in the mindfulness condition.

**Table 3 table3:** Other assessments.

Demographics, medical history, and control factors	T0^a^	T1/T1’	T2/T2’	T3
Age, gender, education, family status, nationality, time since diagnosis, time since previous treatment, fatigue duration, psychological counseling in the past, comorbidity.	a			
Cancer type, cancer treatment, perceived life threat of cancer (7-point Likert scale), known heredity of cancer (yes/no/don’t know), former experience with attention focusing exercise (yes/no), religious beliefs, perceived social support (Multidimensional Scale of Perceived Social Support [77]: 12 items on a 7-point Likert scale).	b			
Medication use, substance use (caffeine, nicotine, alcohol, drugs), quality of life (1 item on a 0-10 NRS).	a	x	x	x
Pain intensity and limitations by pain (2 items on a 7-point Likert scale), body mass index.	b	x	x	x
Life events since previous assessment, professional help received for fatigue outside the scope of the study protocol.		x	x	x
Perceived effectiveness of the intervention (5 items of which 1 item 0-10 NRS and 2 yes/no questions), perceived social support in following the intervention (1-10 NRS).		x		
Social desirability: 6 selected items from the Balanced Inventory of Desirable Responding [78] on 5-point Likert scale.			x	

^a^Baseline assessment T0 consists of 3 time-points: T0a: before eligibility check; T0b: after inclusion; and T0c: after randomization.

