**Figure 5 figure5:**
[figure not shown]
Simplified representation of a correlated growth model in which Iy and Sy represent the intercept and slope factors of the latent growth model of the outcome parameter, and Iz and Sz represent the latent growth factors of the mediator. H1-4 represent the 4 subhypotheses of Step 6. All indicators have been left out for clarity.

###### Step 7

The next step in studying potential working mechanisms is a single-step, multiple-mediation analysis using structural equation modeling [104-106]. By estimating such a model, we expect to obtain a comprehensive model for all the working mechanisms of the intervention. It should be noted that this model assumes that an intervention works in the same way for all participants in a particular group [107]. Again, data from both semesters will be used.

A separate model will be tested for each intervention. Each model will have the following paths (Figure 6), where X=independent variable (1/0 for specific intervention vs control group), Y=outcome variable (difference score T2-T0b of the primary outcome measure), and Z=mediator:

a: X regressed on Z.b: Z regressed on Y;c’: direct effect of X on Y.

For each experimental intervention, the starting model will consist of all the significant primary mediators of Step 6 that have also been assessed in the control group. In other words, the factors that have shown to be mediators in the correlated growth model will be the starting point for this model. The models will then be complemented with the secondary mediating factors described in Textbox 2. Mediating factors for which the indirect effect (a × b) is insignificant will be removed stepwise, after which a final model will be created.

Model fit, standardized path coefficients—including indirect effects—and the total effect of at least the first and final models will be reported with 95% confidence intervals.

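### Step 7 leaves the mediator-to-fatigue path open to confounding by baseline variables the trial already records, so it can credit inert factors that therapy changes, or hide true mediators

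*Protocol article*

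**What the plan says.** The Introduction (Mediators) sets the aim: "Therefore, the second objective of this study will be to identify the working mechanisms underpinning the interventions". The same section says the knowledge is meant to guide shifting the focus of an intervention or shortening it.

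Step 7 defines the model. It opens with "Each model will have the following paths (Figure 6" and then lists "a: X regressed on Z.b: Z regressed on Y;c’: direct effect of X on Y". X is the specific intervention versus control; the rest is defined as "Y=outcome variable (difference score T2-T0b of the primary outcome measure), and Z=mediator". The retention rule is "Mediating factors for which the indirect effect (a × b) is insignificant will be removed stepwise, after which a final model will be created". The one assumption Step 7 acknowledges is that the intervention works in the same way for everyone in a group. It does not mention that the mediator-fatigue relation must be free of common causes.

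Several plausible common causes are recorded:
- Distress (HADS, PANAS): "Mental health will be assessed at T0a, T1, T2, and T3".
- Pain, from T0b: "Pain intensity and limitations by pain (2 items on a 7-point Likert scale), body mass index".
- Comorbidity and time since previous treatment, at T0a (Table 3).
- From T1 only: "Life events since previous assessment, professional help received for fatigue outside the scope of the study protocol".

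The only covariate rule is under Descriptives. Covariates are added if mean fatigue severity differs significantly across baseline descriptives.

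**The concern.** Participants are randomized to a therapy, not to a level of mindfulness, sleep quality or sense of control. Someone with more distress or pain may gain less on the mediator and also lose less fatigue, whether or not the mediator does anything. Without that common cause in the model, its influence is absorbed into b, and so into a × b and c'.

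The article itself supplies candidates. Under Eligibility it treats comorbid somatic disease as a possible cause of fatigue and chooses to include such patients. Textbox 3 expects comorbidity, time since last treatment, baseline sense of control and baseline sleep quality to predict the fatigue response, and the last two are also candidate mediators. Step 6, which selects the starting factors, rests on correlated growth without covariates, so it does not filter out confounded factors.

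At stake is the second objective: a therapy could be shortened or refocused around a factor that transmits nothing, or a real mechanism could be discarded.

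**Working it through.** **Inputs from the article.** Power Analyses: 330 participants in three arms, so 110 per arm. Attrition reproduces: 110 × 0.70 = 77 per experimental arm and 110 × 0.85 = 93.5, given as 94, in control. The nearest stated mediator figure is approximately 254 participants (six factors, f2 = .08, alpha = .05/6, power .80). A joint F test of six predictors gives 252, so that figure is not in dispute.

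**Assumed inputs.** Treatment effect on the mediator a = 0.5 SD. True b = 0, an inert factor. One common cause U with standardized paths of size u = 0.2, 0.3 or 0.4 to mediator change and to fatigue change. Significance of a × b is judged by both a and b being significant at .05.

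**Algebra.** Let Z = 0.5X − uU + e and Y = c'X + uU + e, with unit variance within arms.
- Within-arm covariance of Z and Y: (−u)(u) = −u².
- Apparent b = −u²/1 = −u², although the true b is 0.
- Apparent indirect effect = 0.5 × (−u²), that is −0.02, −0.045 and −0.08 SD for u = 0.2, 0.3 and 0.4.

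**Simulated share of trials retaining an inert factor, 77 vs 94:**

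| u | One mediator | Four mediators, per factor | Four mediators, at least one |
|---|---|---|---|
| 0.2 | about 8% | about 7% | about 25% |
| 0.3 | about 19% | about 13% | about 45% |
| 0.4 | about 51% | about 26% | about 73% |
| U in both equations | 4-5% | 4-5% | roughly 13-19% |

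The four-mediator columns describe the starting model, before stepwise removal. With six mediators and u = 0.4, the per-factor rate is about 19%.

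**Sensitivity, one mediator:**
- a = 0: at most 5% unadjusted, even at u = 0.5. The problem needs a factor that therapy moves.
- a = 0.3: 4%, 11% and 27% unadjusted for u = 0.2, 0.3 and 0.4, and about 3% adjusted.
- a = 0.5 with the covariate measured at reliability 0.8: 4-13% after adjustment, for u up to 0.5. Measurement error leaves some bias.
- Opposite sign: with true b = −0.25 and confounding of 0.5 acting the other way, detection of the real mediator is 5% unadjusted and 86% adjusted. With no confounding it is 81%.

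**The existing covariate rule.** It is triggered by differences in fatigue severity, not by any relation to a mediator. It is not tied to Step 7, and it names neither pain nor comorbidity. Confounding of b requires no baseline imbalance between arms, so a check for imbalance would not detect it.

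**The case against.** **A condensed article leaves covariates to a fuller plan.** The article says its plan is written in general terms, and Step 7 does not say that covariates are forbidden. That has some force. But Step 7 does fix the variables, the paths and the removal rule, and the Discussion describes all methods as now predetermined. Followed as written, path b is unprotected.

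**The plan is not without covariates.** A reader might infer from Step 7 that it is. The documents do not support that. The Descriptives rule covers time since end of treatment and baseline levels of the outcome variables, so it could admit distress. It does so only if its significance trigger fires.

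**A single-mediator calculation overstates the per-factor rate.** This stands. Step 7 is a multiple-mediation model, and the other mediators partly stand in for the common cause; hence 26% rather than 51% at u = 0.4. The chance that some inert factor passes is higher, though.

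**Fatigue change cancels stable effects.** It does so for effects on the level of fatigue. Common causes of change remain, and Textbox 3 expects comorbidity to be one. It does not say this of pain or distress.

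**Larger samples.** A reader might redo the calculation at 110 vs 94, because Step 7 uses both semesters. The article's figures do not support independent groups of that size: 94 × 0.70 = 66 second-semester completers, about 33 per therapy, and 77 + 33 = 110. About 33 of the 110 are the same people as the controls. In the other direction, the expected 10% exclusion for recurrence gives about 69 vs 84, where the single-mediator rate at u = 0.4 is about 44%.

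**Outside help as a confounder.** It is recorded only from T1, so treatment may affect it. It cannot be treated like a baseline covariate.

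**Conclusion.** The point holds in a limited form. Step 7 as specified does not protect the mediator-to-fatigue path, and the plan's conditional covariate rule does not reliably do so. For factors that an intervention changes, common causes of mediator change and fatigue change bias b, a × b and c' in either direction.

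The size depends on assumed confounding. At 0.2 it is minor, about 7-8% against a nominal 5%. At 0.3 to 0.4 it matters: 19-51% with one mediator, and 13-26% per factor with four.

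A reader might infer that Step 7 will name false mechanisms as a matter of course. The documents do not support that: they give no confounding strengths, the false signal nearly vanishes when a = 0, and the bias can equally hide true mediators. The randomized comparison of fatigue in Step 1 is not affected. The change should be made because it serves a stated objective and uses data already in hand.

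**What to change.** In every Step 7 model, put one fixed set of pre-randomization covariates in both the mediator and the outcome equations:
- the T0b value of each mediator where one was measured (credibility and expectancy are first measured at T0c, and working alliance has no baseline value);
- HADS (T0a);
- pain intensity (T0b);
- comorbidity (T0a);
- time since last treatment (T0a).

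State that the indirect effects still assume no unmeasured mediator-outcome confounding. Use outside professional help and life events, recorded only from T1, at most in a labelled sensitivity analysis of the final model, with the caveat that treatment may affect them.

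The cost is a change of wording in the analysis plan and about five degrees of freedom per equation. No new data are needed. Some residual confounding will remain through measurement error in the covariates.

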#### Effect Predictors

Although we expect that, in general, both interventions are effective, personal factors, medical factors, and demographics may determine the effect that each intervention has on fatigue [41]. We do not expect all individuals to benefit similarly from the interventions. Therefore, studying potential predictors of each intervention’s effect will give us important input to inform both patients and caregivers and allow them to set reasonable expectations.

CCRF has a multifactorial character (eg, physical, cognitive, motivation); therefore, studying the effect predictors of 2 theoretically differing interventions simultaneously might also reveal differentiating predictors for both therapies. By applying such knowledge carefully, the overall effectiveness of interventions that aim to reduce CCRF can be increased.

## Methods

### Design

A randomized controlled trial is performed including 3 parallel conditions: 2 experimental conditions (AAF and eMBCT) and a minimal intervention control condition. The intervention period is 9 weeks for all 3 conditions. Both experimental conditions are made as similar as possible in terms of time-investment and contact intensity with the therapist. Outcomes are self-reported and are Web-assessed at baseline (T0), 2 weeks post-intervention (T1), and at 6 months (T2) and 12 months (T3) after baseline. Figure 3 shows a schematic summary of the trial design.

The baseline assessment consists of 3 time-points: (1) T0a, the assessment to check eligibility; (2) T0b, the main baseline assessment taken after the eligibility check and informed consent, but naive of condition; and (3) T0c, directly after randomization for assessing the participant’s credibility and expectancy about the condition. All participants are invited to fill out short questionnaires in weeks 1, 2, 3, 4, 6, and 9 (Mi) of the intervention period in order to study mediation of the interventions.

After T2, patients in the control condition are offered 1 of the 2 experimental interventions, again in a research setting. Please note that the first 4 participants of this trial were randomized to 1 of the experimental conditions for the second semester, but to minimize dropout, all other patients will be allocated based on their own preference. During this second intervention period, these participants will again be assessed in weeks 1, 2, 3, 4, 6, and 9 (Mi’), the second week after the intervention (T1’), and 6 months after the second allocation (T2’). Participants in the control condition that are preferentially allocated to eMBCT after T2 do not wear the accelerometer during the second semester.

The protocol allows delay within the intervention period of a maximum of 2 weeks in case of, for example, illness or holiday. For all participants, the duration of their participation is approximately 12 months. Additional qualitative feedback will be obtained through explorative interviews with a subset of participants in the experimental condition shortly after T1 or T1’.

This trial was approved by the Twente Medical Ethical Committee (Enschede, the Netherlands) under number P12-26 and has been registered at The Netherlands National Trial Register under number NTR3483 [42].

**Figure 3 figure3:**
[figure not shown]
Flow chart of trial design. CS = cancer survivor; MD = medical doctor; PA = physical activity; T0(a-c)-T3 are the main assessments; Mi and Mi' represent assessments in week (i =) 1, 2, 3, 4, 6, and 9 of the intervention. For addressing the primary research questions of effectiveness, only data from the first semester will be used.

### Study Sample

#### Recruitment

Participants are recruited in the Netherlands by advertisements in the newsletters of patient associations (both digital and print), on relevant websites, in regional newspapers, and through social media. Furthermore, participants also are recruited through oral presentations given to cancer patients and in other cancer-related seminars and symposia for patients, caregivers, or both.

Social media and online advertising can be strong tools for reaching a large group of people [43] or even specific patients [44,45]. However, the sample might be younger, more highly educated, and might comprise more females compared to the Dutch CCRF population [46]. However, it will lead to a sample that represents the targeted population for such Internet interventions, and we are likely to include participants who would not have opted for therapy that includes traveling to a health care facility.

#### Eligibility

The following criteria are used to check eligibility for participation in the trial:

Completion of a curative-intent treatment for cancer at least 3 months ago (checked by participant’s medical doctor). For this study, surgery, chemotherapy, radiotherapy, immunotherapy, and/or stem cell transplantation are considered treatment. However, hormonal therapy, the use of anti-inflammatories, and monitoring visits are not considered treatment for this study.Patient has been suffering from severe fatigue for at least 3 months.Patient scores 35 or higher on the fatigue severity subscale of the Checklist for Individual Strength (CIS).Aged 19 years old or older.At least 18 years old at disease onset.Capable of reading and writing in the Dutch language and of using the Internet (implicit eligibility criterion accounted for during registration, but not checked explicitly).

If patients meet 1 or more of the following criteria, they are excluded from participation:

Indication of current disease or tumor activity (checked by the participant’s medical doctor).Current or former severe psychiatric morbidity, for example, major depression, psychosis, or schizophrenia (checked by the participant’s medical doctor).Being dependent on a wheelchair for daily activity (self-report).Recurrence of cancer during the course of the study (self-report).Current substance abuse, except for smoking.Previously attended the eMBCT of the Helen Dowling Institute.

In addition to the mentioned exclusion criteria, please note that:

Mild depression is not an exclusion criterion. A score of 20 points or higher on the Hospital Anxiety and Depression Scale (HADS) during baseline is considered indicative of depression [47]. Therefore, if the patient scores 20 points or higher, he or she will be contacted by a psychologist from the Helen Dowling Institute to determine whether the participant has suicidal ideation or suffers from other severe psychiatric morbidity. A participant will only be excluded if, according to the involved psychologist, that is the case.Comorbid somatic diseases—such as cardiovascular diseases, cerebrovascular diseases, diabetes, hypertension, and arthritis that are not treatable but are a possible cause of fatigue—are not exclusion criteria but will be registered during the study. Although this choice will probably lead to an underestimated effect size compared to studies that do exclude patients with comorbidities, we expect that such a sample will lead to a better representation of the CCRF population.Participants are requested not to take part in any other therapy directed at overcoming fatigue during the study.Data of participants who report pregnancy or recurrence of cancer during the course of the study will be excluded from analysis since the fatigue they experience cannot be considered to be of a chronic character according to our definitions. However, if requested, these patients will be allowed to finish the intervention.

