#### Pre-Analysis

##### Power Analyses

The sample size for analyses for data relating to the primary objective has been calculated for a repeated measures analysis of variance: based on an alpha of .05, a minimal detectable effect size of f2=.15, and a power of .80, a total number of 55 participants [80] is required in each group to answer the primary research question of this study in a statistically valid manner.

We expect to be able to include 330 eligible participants within a period of 2 years, based on a mean of 3.7 intakes per week for the eMBCT of the Helen Dowling Institute in 2011. An estimated attrition of 30% of the participants during both experimental interventions and 15% during the minimal intervention control condition [51] would leave us with 77 participants in each experimental group and 94 participants in the control group at T2. Again, we expect a dropout rate of 30% during the second semester. Such a dropout would leave a total of 110 participants completing each experimental intervention. Ten percent of the participants may have to be excluded from the analyses because of recurrence or diagnosis of metastasis. That would result in 198 participants that complete the full trial. We expect that this number will be enough for testing the 6 mediating factors or effect predictors: A classical, conservative power calculation (analysis of variance for testing 6 mediators or effect predictors with an intermediate effect size (f2=.08), corrected according to Bonferroni (alpha=.05/6), and at a power of .80 [81]) would result in approximately 254 participants being needed. We expect that the actual power when including 198 participants, and not the required 254 participants, will be great enough to detect up to 6 mediators or effect predictors with the use of Bayesian statistics [76]. Bayesian statistics allow analysis on small sample sizes [76,77], as more power can be generated with the use of prior information which is incorporated in the model that is being tested. Various papers describe comparisons between traditional null hypothesis testing and Bayesian estimation [82-85]. For this study, prior knowledge is available for many parameters, such as the effects of mindfulness in cancer survivors [23,25,66,86] and the role of working alliance in online interventions [87]. Examples of these methods can be found in both applied psychology and social science articles [88-92].

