##### Descriptives

Quantitative analyses will be conducted on an intention-to-treat basis. A flow diagram following the CONSORT guidelines will be included. Descriptive statistics will be calculated and presented. Independent samples’ t-tests and χ^2^ tests will be performed to check for baseline differences between the respective experimental conditions and the control condition with respect to demographic variables (eg, family status, age, gender, and level of education), time since end of treatment, and baseline levels of the outcome variables. If we find statistically significant differences in the mean of fatigue severity across baseline descriptives, dummy variables will be added to the model as covariates to control for these differences.

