#### Core Analysis

##### Effectiveness

###### Overview

Five steps will be taken to evaluate the effectiveness of both interventions, which are explained here in a generic way. The specific hypotheses on the effectiveness of the interventions in our study are shown in Textbox 1.

Hypotheses on effectiveness.
*Primary outcome*
In both experimental conditions:Fatigue severitydecreases during the intervention, andremains decreased after 6 months.After 6 months, fatigue severity has decreased significantly more compared to the control condition.After 6 months, more participants show a clinically relevant reduction of fatigue severity compared to the control condition. A patient is considered clinically improved if he or she has a reliable change index of more than 1.96, according to the reliable change index, and the end score has to be within the normal range, that is a score < 1 standard deviation above the mean of a normative group [94] (ie, a score < 30.4 on the CIS fatigue severity subscale [51]).
*Secondary outcomes*
For both interventions we expect that:After 6 months, mental health and work ability have improved more than in the control condition.After 12 months, fatigue severity, work ability, and mental health remain improved in both intervention groups.Improvements in mental health and work ability after 6 and 12 months are related to reductions in fatigue severity.Return to work and reduced absenteeism will be studied as explorative outcomes.

###### Step 1

Overall effectiveness will be tested in an intention-to-treat analysis by a multiple group latent growth model [79] using data from the first semester. This technique allows individuals to have an individual growth trajectory over time and compensates for missing data in an elegant way.

Since different growth patterns are expected for the pre-intervention period, the intervention period, and the post-intervention period, we will apply piecewise growth modeling so that a slope factor will be estimated for each of the 3 periods (Figure 4). Initial intercepts will be configured to represent the T0b score. This intercept and the pre-intervention slope factor will be constrained to be equal between all 3 conditions (and this assumption will be checked), whereas the subsequent slope factors will be estimated separately for the 3 conditions.

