**Figure 4 figure4:**
[figure not shown]
Simplified representation of a piecewise linear latent growth model, with latent intercept factor (I), latent slope factors preintervention (S(pre)), during the intervention (S(int)), and postintervention (S(post)), and 7 indicators Y. Error terms, correlation coefficients, and covariances are left out.

**Table 5 table5:** Growth factor estimates of 4 different latent growth models.

	Fixed loadings	Time-varying loadings
Piecewise, linear	Mean: I, S(pre), S(int), S(post) Variance: I, S(pre), S(int), S(post)	Mean: I, S(pre), S(int), S(post) Variance: I, S(pre), S(int), S(post)
Quadratic	Mean: I, S, Q Variance: I, S, Q	Mean: I, S, Q Variance: I, S, Q

###### Step 2

The effect size of both experimental interventions will be calculated according to recommendations in Feingold (2009) [95] for both primary and secondary outcomes.

###### Step 3

The proportion of participants who make clinically relevant progress on the primary outcome will be calculated for all 3 conditions; again, in an intention-to-treat analysis. Percentages and standard deviations of the reliable change index will be presented.

###### Step 4

A latent growth model will be built of the primary outcome, in which the outcome measures that have been measured at T3 will also be included, as distal outcomes of changes in the primary outcome during the first semester.

###### Step 5

A growth mixture model (GMM) will be used to further explore differences between individuals, and more specifically to identify subpopulations (latent classes) with homogeneous growth trajectories of the primary outcome within the experimental groups. The Bayesian information criterion will be used for model selection [96].

If convergence considerations allow, this model will be adjusted to allow covariance of the growth factors in order to acknowledge individual variation around the estimated growth trajectories. The trace plots will be inspected to check whether the models have converged to global solutions and a set of diverse starting values will be used. For more information on these analyses, we refer to an introduction to GMM and latent class growth analysis by Jung and Wickrama [97] and examples of similar analyses in the field of Internet interventions [98] and cancer patients [41].

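### Participants who report cancer recurrence or pregnancy after randomization are left out of the analysis, which contradicts the declared intention-to-treat basis

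*Protocol article*

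**What the plan says.** The protocol article treats recurrence and pregnancy during the study in three places.

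- **Eligibility, exclusion list:** one entry reads "Recurrence of cancer during the course of the study (self-report". It stands beside criteria that are checked before entry.
- **Eligibility, closing notes:** "Data of participants who report pregnancy or recurrence of cancer during the course of the study will be excluded from analysis". The reason given is "since the fatigue they experience cannot be considered to be of a chronic character according to our definitions". The same note lets these participants finish the intervention if they ask to.
- **Power Analyses:** "Ten percent of the participants may have to be excluded from the analyses because of recurrence or diagnosis of metastasis". Pregnancy is not mentioned there.

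The analysis plan declares its basis three times.

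- **Descriptives:** "Quantitative analyses will be conducted on an intention-to-treat basis".
- **Effectiveness, Step 1 (primary analysis):** "Overall effectiveness will be tested in an intention-to-treat analysis by a multiple group latent growth model", with data from the first semester.
- **Effectiveness, Step 3 (clinically relevant change):** "again, in an intention-to-treat analysis".

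The article does not define a modified intention-to-treat set, does not keep data up to the event, and does not plan an analysis that includes these participants.

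**The concern.** Recurrence and pregnancy during the study cannot be known at entry. Leaving out participants because of them conditions the comparison on something that happens after allocation, so the analysed groups are no longer the randomized groups. Two analysts following the article could build different primary data sets: one from the exclusion note, the other from the intention-to-treat statements.

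The rule is also broader than its reason. If fatigue stops being chronic by the trial's definition once cancer recurs or pregnancy begins, that speaks to scores from about that time onward. The rule has no time limit and removes the participant's earlier scores as well.

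At stake are the membership of the primary analysis set and the right to call the result intention-to-treat.

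**Working it through.** **1. The plan's own count.** Inputs from Power Analyses: "We expect to be able to include 330 eligible participants within a period of 2 years", attrition of 30% in each experimental arm and 15% in control, a further 30% in the second semester, then 10% excluded.

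- Per arm: 330 / 3 = 110.
- Each experimental arm at T2: 110 × 0.70 = 77.
- Control at T2: 110 × 0.85 = 93.5 (stated as 94).
- Former controls completing an intervention: 93.5 × 0.70 = 65.45.
- Completers of either intervention: 77 + 77 + 65.45 = 219.45, about 220 (stated as 110 per intervention).
- After the 10% exclusion: 219.45 × 0.90 = 197.5, stated as 198.

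The figure of 198 is reproduced. The exclusion is therefore built into the planning, but it is applied to completers pooled over both semesters, in the argument about mediators and effect predictors. It is not applied to the T2 arms of 77, 77 and 94. The share lost from the primary contrast cannot be read from the article.

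**2. Timing.** Design gives about 12 months of participation and places T2 at 6 months. The caption of Figure 3 and Step 1 limit primary effectiveness to first-semester data. The window for a disqualifying report thus runs about 12 − 6 = 6 months beyond the last score used in the primary analysis. A report in that period removes primary-outcome scores from T0b to T2 that were all recorded before it. A report before T2 also removes the scores that preceded it.

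**3. Possible bias.** Let q be the excluded share in an arm, and D the mean fatigue of those excluded minus that of those retained. The full-arm mean equals the retained mean plus q × D. For arms a and c:

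full contrast − retained contrast = q_a × D_a − q_c × D_c.

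With a common D this is (q_a − q_c) × D. The article gives neither q by arm nor D, so all values below are assumptions.

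| Difference in excluded share | D | Shift |
|---|---|---|
| 0 | any common value | 0 |
| 2 percentage points | 5 CIS points | 0.02 × 5 = 0.1 points |
| 6 percentage points | 10 CIS points | 0.06 × 10 = 0.6 points |
| 4 percentage points (12% vs 8%) | 0.5 to 1.0 SD | 0.02 to 0.04 SD |
| 10 percentage points (15% vs 5%) | 0.5 to 1.0 SD | 0.05 to 0.10 SD |

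The CIS fatigue severity subscale runs from 8 to 56.

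**4. Chance imbalance.** If 10% of 110 were excluded in each arm (an assumption), the difference in excluded share would lie within ±1.96 × √(2 × 0.1 × 0.9 / 110) = ±0.079 in 95% of trials. An imbalance of up to about 8 percentage points is possible by chance alone. That adds noise; it is not systematic bias.

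**The case against.** The rule is published in advance and reasoned, and the data are set aside, not destroyed. A fuller analysis plan may define the set. Even so, the article itself states two rules for the same analysis that cannot both hold.

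Several stronger readings are tempting, and the documents do not support them.

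- **That each arm loses 10% at T2.** This would give 77 × 0.9 = 69.3 and 93.5 × 0.9 = 84.2, and a variance factor of 1 / 0.9 = 1.11. The 10% is a contingency, covers recurrence or metastasis only, and belongs to the pooled two-semester count. Even 69 and 84 would exceed the stated 55 per group, so the issue is validity, not power.
- **That reporting differs by arm.** Participants are unblinded and recurrence is self-reported. In the first semester only the experimental arms have weekly therapist contact, and expected attrition is 30% against 15%. But all arms receive the same Web assessments at T1, T2 and T3, and those who withdraw are phoned whatever their arm. No section makes the therapist the route for reporting. More contact would raise reporting in the experimental arms and more attrition would lower it, so the net direction is unknown.
- **That every score before the report is sound.** A report dates disclosure, not onset. Some earlier scores may already reflect recurrence.

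It is also fair to say that setting observed scores after the report to missing is not intention-to-treat. That analysis targets a hypothetical outcome free of the event, and it assumes the missing scores are missing at random. It therefore belongs among the sensitivity analyses.

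**Conclusion.** The contradiction stands. Followed as written, the exclusion note gives a primary analysis set that is not intention-to-treat, while Descriptives and Steps 1 and 3 say that it is. The rule also removes first-semester scores that its stated reason does not reach, most clearly when the report comes after T2.

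The effect on the estimate is uncertain and probably modest. It is zero if the excluded share and the prognosis of those excluded are the same across arms. Under the assumptions shown it is 0.1 to 0.6 CIS points, or up to 0.10 SD with a 15% versus 5% split. No systematic difference between arms has been shown. The reason to act is that the primary set should be unambiguous and should preserve the randomized comparison.

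**What to change.** 1. Do not exclude participants from the effectiveness analysis because of a post-randomization report of recurrence or pregnancy. Analyse all their recorded first-semester fatigue scores in Step 1, and keep them in the Step 3 proportions. Call this the intention-to-treat analysis.
2. Add two sensitivity analyses: one with scores after the report set to missing, stating the hypothetical estimand and the missing-at-random assumption; and one with the planned full exclusion, labelled modified intention-to-treat.
3. Take recurrence during the study out of the list of entry criteria. Reconcile that list with the closing note on whether these participants leave the study or may finish the intervention. Which of the two applies is a clinical matter on which this review takes no position.
4. Report recurrences and pregnancies by arm, with timing relative to T2.

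This concerns recurrence and pregnancy only. The rule in Randomization that does not count participants without T0c as included is a separate departure.

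The cost is plan wording and two extra model runs, with no new data. The article says it was submitted before any data were analysed, so the change can still be made credibly. The downside is that some scores affected by recurrence or pregnancy stay in the primary set and may slightly dilute the effect.
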